**Secondary efficacy endpoints**

**All-Cause Mortality at day 40 (ACM20)**

Death rates will be estimated at day 40 within each group.

The difference in ACM20 rates and the odds ratio will be estimated along with their asymptotic and exact 95% confidence intervals. p-values from the chi-square and exact Fisher test will also be provided.

The All-cause mortality at Day 40 will also be analyzed in a Logistic regression model including treatment, BMI (>30 , <30) , Age (>60 , <60) and baseline respiratory distress status for each primary component (moderate or not). The adjusted odds ratio with its 95% CI for treatment will be estimated in this model.

Subgroup analyses will also be analyzed in the same logistic regression model including treatment, each factor (separately) and a term for treatment-by-factor interaction.

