### 11.1 General considerations

In general, summary tabulations will be presented by treatment arm and will display the number of observations, mean, standard deviation, median, minimum, and maximum for continuous variables, and the number and percent per category for categorical data. The Kaplan-Meier survival curves and 25th, 50th (median), and 75th percentiles will be provided along with their 2-sided 95% confidence intervals (CIs) for time-to-event data.

The nominal one-sided alpha level of significance considered for statistical tests will be 0.025.

As this is essentially an estimation study, no adjustment for multiplicity will be proposed.

Methods for handling missing data will be further detailed in the SAP.

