### 11.4 Sample Size Determination

As this is essentially an exploratory study which aim is to estimate the treatment difference in order to better design the future trials, the sample size cannot be justified on a formal power calculation based on a reasonable expected difference.

60 (sixty) patients are considered sufficient to estimate the treatment effect on the efficacy parameters.

As a rough order of magnitude, if the true death rate is assumed to be 0.4 in the placebo group, then a true death rate of 0.10 should be assumed to achieve at least a 80% power to detect this difference in rates at the 1-sided alpha level of 0.025, using an unpooled variance Z test. If the true death rate is assumed to be lower, such as 0.3 in the placebo group, then a true death rate of 0.04 should be assumed to achieve at least a 80% power to detect this difference in rates at the 1-sided alpha level of 0.025, using an unpooled variance Z test.

Assuming a dropout rate of 12%, 68 patients will be enrolled in this study.

With regard to the primary safety endpoint, 60 (2X30) patients randomized will be sufficient to observe in the ACT017 arm at least one serious adverse event which incidence is greater than or equal to 5% with a probability of at least 79%.

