**Overall survival**

Overall Survival will be defined as the time from the date of randomization to the date of All-cause death.

Patients without documentation of death at the time of analysis (i.e. lost to follow-up) will be censored at the last date they were known to be alive.

Kaplan-Meier (KM) survival curves will be provided by treatment. KM survival medians with their 2-sided 95% CIs will be provided (if estimable) for each treatment group. KM

estimates at Days 1, 2, 3, 4, 14, 20 and 40 will be provided within each group of treatment. A log-rank test will be used to compare treatment arms.

In addition, a Proportional Hazard (PH) Cox model adjusting for treatment will be fitted to estimate the treatment effect expressed in terms of a hazard ratio with the 95% CI and p-value.

Subgroup analyses:

If feasible (i.e. when subgroup sizes are sufficient), analyses of OS will be performed by BMI (  $<30$  vs  $\geq 30$  ), Age (  $< 65$  vs  $\geq 65$  ), by baseline WHO-Covid-19 scale, comorbidity, concomitant medications, considering a PH Cox regression model including treatment, each studied factor (considered separately) and a term for treatment-by-factor interaction. The treatment effect (Hazard ratio) by subgroup will be estimated in this model.

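### The Day-40 mortality logistic model and its interaction models are too sparse for the expected deaths, and the age, BMI and medication factors are not cleanly defined

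*Protocol*

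**What the plan says.** All locations are in the Protocol.

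- **Adjusted mortality model** (section 11.5.1, All-Cause Mortality at day 40). After the unadjusted rate difference and odds ratio, mortality is also analysed in a "Logistic regression model including treatment, BMI (>30 , <30) , Age (>60 , <60) and baseline respiratory distress status for each primary component". Each component status is coded as moderate or not.
- **Interaction models** (same place). Subgroups are handled by a logistic model "including treatment, each factor (separately) and a term for treatment-by-factor interaction". No feasibility condition is attached. The subgroup analyses of the primary endpoint, overall survival and the WHO scale all carry one.
- **Overall survival** (section 11.5.1). A Cox model gives the treatment hazard ratio. Its subgroup factors include "comorbidity, concomitant medications, considering a PH Cox regression model including treatment, each studied factor".
- **Death rates** (section 11.4). The first pair reads "if the true death rate is assumed to be 0.4 in the placebo group, then a true death rate of 0.10 should be assumed". The second pair sets 0.30 on placebo against 0.04 on active treatment, again for 80% power. The protocol presents these as a rough order of magnitude.
- **Age cut.** For primary-endpoint subgroups it is 65 in the synopsis (Statistical Methods) and 60 in section 11.5.1. It is 60 in the mortality model, and 65 for overall survival and the WHO scale.

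**The concern.** The adjusted model asks for six coefficients from a small number of deaths. Estimates fitted by ordinary maximum likelihood are then unstable. If no patient on active treatment dies, the treatment odds ratio and the Cox hazard ratio have no finite value. The interaction models split the same deaths over four cells, so they fail sooner.

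The factors themselves also need repair. The mortality model names only values strictly above and strictly below 60 (age) and 30 (BMI), so a patient exactly at a boundary belongs to no group. Two sections give different age cuts for the same subgroup analysis. Concomitant medications, unlike the WHO score beside them, are not described as baseline. Drugs started after randomisation can reflect how the patient fared, and subgrouping on them would undo the randomised comparison.

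**Working it through.** **Inputs.** 30 patients per arm (section 11.4, 2 × 30); 1:1 allocation (section 11.2); death rates 0.40 v 0.10 and 0.30 v 0.04 (section 11.4), taken here as Day-40 rates, which is an assumption; "The nominal one-sided alpha level of significance considered for statistical tests will be 0.025" (section 11.1). Model terms: treatment, BMI, age, and one status for each of the three non-death components (respiratory rate, SpO2, PaO2/FiO2), making six plus an intercept.

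**1. The plan's own power figures reproduce.** Unpooled Z test: power = Φ(difference / √[(p₁q₁ + p₂q₂)/30] − 1.96).
- 0.40 v 0.10: 0.30 / √[(0.24 + 0.09)/30] = 0.30/0.1049 = 2.860; Φ(0.900) = 81.6%.
- 0.30 v 0.04: 0.26 / √[(0.21 + 0.0384)/30] = 0.26/0.0910 = 2.857; Φ(0.897) = 81.5%.

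Both meet the stated 80%.

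**2. Deaths per term.**
- 30 × (0.40 + 0.10) = 15.0 deaths; 15.0/6 = 2.5 per term.
- 30 × (0.30 + 0.04) = 10.2 deaths; 10.2/6 = 1.7 per term.

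With 34 per arm (all 68 enrolled) the figures are 17.0 and 11.6 deaths, or 2.8 and 1.9 per term.

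**3. No finite treatment estimate.** This occurs when the active arm has no deaths: (1 − p)³⁰.
- 0.90³⁰ = 4.2%.
- 0.96³⁰ = 29.4% (0.96³⁴ = 25.0% with 34 per arm).

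**4. Interaction models.** With a factor splitting each arm exactly 15/15, the chance that at least one of the two active-arm cells has no deaths is 1 − (1 − (1 − p)¹⁵)²: 36.9% at 0.10 and 79.0% at 0.04. Simulating random splits and counting any cell with no deaths or only deaths gives:

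| Factor split (assumed) | 0.40 v 0.10 | 0.30 v 0.04 | 0.40 both arms | 0.30 both arms |
|---|---|---|---|---|
| 50/50 | 39% | 80% | 0.5% | 3% |
| 40/60 | 41% | 81% | 1% | 5% |
| 30/70 | 48% | 84% | 5% | 12% |
| 20/80 | 63% | 89% | 19% | 30% |

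The failures come mainly from the low active-arm rate.

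**5. Boundary patients.** With age in whole years, and age distributions assumed uniform or roughly normal around 60, 1.6–3.8% of patients are exactly 60. That is about 1 to 2 of 60 patients, with a 62–90% chance of at least one. The BMI count depends on rounding and was not estimated.

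**6. Definitions side by side.**

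| Analysis | Age cut | Boundary value assigned? | Concomitant medications a factor? |
|---|---|---|---|
| Primary endpoint, synopsis | 65 | yes | yes |
| Primary endpoint, section 11.5.1 | 60 | yes | yes |
| Day-40 mortality | 60 | no | no |
| Overall survival | 65 | yes | yes |
| WHO scale | 65 | yes | yes |

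**The case against.** **The adjusted model carries little weight.** The unadjusted difference and odds ratio, with asymptotic and exact intervals and Fisher's test, come first, and survival also has Kaplan–Meier curves and a log-rank test. The study is described as exploratory estimation. This stands, and it limits the severity.

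**The fitting method may be settled in the SAP.** Section 11.5.1 leaves full details to the SAP, which could specify penalisation. That is fair for the fitting method. The protocol itself, however, fixes the six terms and the unconditional interaction models.

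**The rates are illustrative.** They are effects needed for 80% power, not forecasts, and are not tied to Day 40. This also stands; with equal death rates the interaction models seldom fail at moderate splits.

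**Stronger readings that a reader might infer:**
- *That the six-term model usually cannot be estimated.* Simulated separation of at least one term ranges from 5% to 62% (0.40 v 0.10) and from 32% to 77% (0.30 v 0.04), depending on covariate prevalences that the protocol does not give. Separation of a covariate alone does not make the treatment odds ratio infinite. For the treatment effect, the supported figures are 4% and 29%.
- *That boundary patients will be dropped.* The inclusive boundaries elsewhere suggest loose drafting, so only the gap in the wording is certain.
- *That a cut-off could be chosen after seeing results.* Section 11 requires the SAP to be final before lock and unblinding.
- *That the mortality model conditions on post-randomisation drugs.* Its named factors other than treatment are all baseline. Medications appear only in other subgroup analyses and are recorded from screening, so a baseline definition remains possible.

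**Conclusion.** The point holds as a sparse-model and drafting problem of low to moderate severity. At the protocol's own rates, six terms rest on 2.5 or 1.7 deaths each. The treatment odds ratio and the Cox hazard ratio have no finite maximum-likelihood estimate in about 4% or 29% of trials. The interaction models are the weakest part: about 39–48% or 80–84% of trials have an empty or full cell for splits between 50/50 and 30/70.

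These figures assume 30 per arm, the section 11.4 rates applied at Day 40, ordinary maximum likelihood and, for the interactions, the assumed splits. The unassigned boundary values and the 60 v 65 contradiction need no assumption. The medication factor is an ambiguity to close, not a demonstrated bias.

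**What to change.** - Name the unadjusted risk difference with exact confidence interval as the main mortality result.
- Fit the adjusted logistic, Cox and interaction models with Firth penalisation and fewer terms, for example treatment, age and one baseline severity term such as the WHO score.
- Run interaction models only where every cell has both deaths and survivors, or under penalisation. A condition on subgroup size alone, as used elsewhere, does not ensure enough deaths.
- Use one age cut-off throughout, in synopsis and body, with the boundary value assigned to one side, and BMI below 30 v 30 or above.
- Define the medication subgroup factor as medications ongoing at randomisation.

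The cost is a wording change in the protocol and SAP and a standard software option, all before unblinding. The price is slight shrinkage of the estimates and fewer adjusted factors.

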**Overall survival**

Overall Survival will be defined as the time from the date of randomization to the date of All-cause death.

Patients without documentation of death at the time of analysis (i.e. lost to follow-up) will be censored at the last date they were known to be alive.

Kaplan-Meier (KM) survival curves will be provided by treatment. KM survival medians with their 2-sided 95% CIs will be provided (if estimable) for each treatment group. KM

estimates at Days 1, 2, 3, 4, 14, 20 and 40 will be provided within each group of treatment. A log-rank test will be used to compare treatment arms.

In addition, a Proportional Hazard (PH) Cox model adjusting for treatment will be fitted to estimate the treatment effect expressed in terms of a hazard ratio with the 95% CI and p-value.

Subgroup analyses:

If feasible (i.e. when subgroup sizes are sufficient), analyses of OS will be performed by BMI (  $<30$  vs  $\geq 30$  ), Age (  $< 65$  vs  $\geq 65$  ), by baseline WHO-Covid-19 scale, comorbidity, concomitant medications, considering a PH Cox regression model including treatment, each studied factor (considered separately) and a term for treatment-by-factor interaction. The treatment effect (Hazard ratio) by subgroup will be estimated in this model.

### **WHO COVID-19 Scale**

The WHO COVID-19 Scale is 9-point ordinal scale and will not be considered as an interval scale. A categorical analysis will be performed.

A descriptive analysis of each category (count and percentage) will be performed by treatment group at each assessment day. The distribution of outcomes on WHO COVID-19 Ordinal Scoring Scale will also be described via plots (e.g., stacked bar plots representing the proportion of subjects in each category, by treatment arm, over time).

The distribution of the 9-point ordinal scale at each post randomization time point will be compared between groups with a Cochran-Mantel Haenszel test using modified ridit scores (i.e. categorical counterpart of the Wilcoxon test) and stratified by baseline WHO COVID-19 status.

In addition, an analysis will be performed on the change from baseline to each time point which will be transformed into a categorized 3-point ordinal scale as follows: worsened, unchanged, and improved. A descriptive analysis of each category (count and percentage) will be performed by treatment group at each assessment day. The distribution of outcomes will also be described via plots (e.g., stacked bar plots representing the proportion of subjects in each category, by treatment arm, over time).

The analysis of the 3-point ordinal scale will be performed with the same approach proposed for the 9-point ordinal scale. The analysis of the binary endpoint will be performed using a Cochran-Mantel Haenszel test (using modified ridit scores) stratified by baseline WHO COVID-19 status.

Missing data will be replaced by the last available value.

Subgroup analyses:

If feasible (i.e. when subgroup sizes are sufficient), analyses of the WHO COVID-19 scale will be performed by BMI (  $<30$  vs  $\geq 30$  ), Age (  $< 65$  vs  $\geq 65$  ), by baseline WHO-Covid-19 scale, comorbidity, concomitant medications with the same approach proposed for the FAS.

**NEWS-2 scale**

NEWS2 is the latest version of the National Early Warning Score (NEWS) updated in December 2017. As the news-2 scale is not an interval scale, a categorical ordinal analysis will be performed. Thresholds on the aggregated score suggested by the Royal College of Physicians will be used to transform the NEWS-2 scale into a categorized scale (called hereafter the “categorized news-2 scale”). Further details on the thresholds will be provided in the SAP.

Missing values of the NEWS-2 scale not due to death will be replaced by the last available news-2 scale value before deriving the category of the categorized NEWS-2 scale. Missing values of the NEWS-2 scale due to death occurring prior to or on day D4 will be imputed in the highest category.

A descriptive analysis of each category (count and percentage) will be performed by treatment group at day D4.

The distribution of the categorized news-2 scale at Day D4 will be compared between groups with a Cochran-Mantel Haenszel test using modified ridit scores (i.e. categorical counterpart of the Wilcoxon test) and stratified by baseline categorized news-2 scale values.

The same analysis will be proposed at other time points (Days 1, 2, 3, 14, 20 and 40).

The distribution of outcomes on the categorized news-2 scale will also be described via plots (e.g., stacked bar plots representing the proportion of subjects in each category, by treatment arm, over time).

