## 18. APPENDICES

### Appendix 1: NEWS-2 Scale

| National Early Warning Score (NEWS)* |       |          |             |             |             |           |            |
|--------------------------------------|-------|----------|-------------|-------------|-------------|-----------|------------|
| PHYSIOLOGICAL PARAMETERS             | 3     | 2        | 1           | 0           | 1           | 2         | 3          |
| Respiration Rate                     | ≤8    |          | 9 - 11      | 12 - 20     |             | 21 - 24   | ≥25        |
| Oxygen Saturations                   | ≤91   | 92 - 93  | 94 - 95     | ≥96         |             |           |            |
| Any Supplemental Oxygen              |       | Yes      |             | No          |             |           |            |
| Temperature                          | ≤35.0 |          | 35.1 - 36.0 | 36.1 - 38.0 | 38.1 - 39.0 | ≥39.1     |            |
| Systolic BP                          | ≤90   | 91 - 100 | 101 - 110   | 111 - 219   |             |           | ≥220       |
| Heart Rate                           | ≤40   |          | 41 - 50     | 51 - 90     | 91 - 110    | 111 - 130 | ≥131       |
| Level of Consciousness               |       |          |             | A           |             |           | V, P, or U |

*Appendix 2: WHO COVID-19 Ordinal Scoring Scale*

| Patient State                          | Descriptor                                            | Score |
|-----------------------------------------------|--------------------------------------------------------------|--------------|
| Uninfected                      | No clinical or virological evidence of infection             | 0            |
| Ambulatory                      | No limitation of activities                                  | 1            |
|                                               | Limitation of activities                                     | 2            |
| Hospitalized
Mild disease   | Hospitalized, no oxygen therapy                              | 3            |
|                                               | Oxygen by mask or nasal prongs                               | 4            |
| Hospitalized
Severe Disease | Non-invasive ventilation or high-flow oxygen                 | 5            |

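### The NEWS-2 comparison is run only on threshold categories, although the planned rank test is valid on the full 0–20 score and could rank death below every survivor

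*Protocol*

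**What the plan says.** NEWS-2 is one of the secondary efficacy endpoints in Protocol section 9.1. Section 11.5.1 (NEWS-2 scale) sets out its analysis:

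- Premise: "As the news-2 scale is not an interval scale, a categorical ordinal analysis will be performed".
- Cut: thresholds on the aggregate score, attributed to a professional body, "will be used to transform the NEWS-2 scale into a categorized scale". The cut-offs themselves are deferred: "Further details on the thresholds will be provided in the SAP".
- Test: a "Cochran-Mantel Haenszel test using modified ridit scores (i.e. categorical counterpart of the Wilcoxon test) and stratified by baseline categorized news-2 scale values", at Day 4 and again at the other listed days.
- Death: missing values "due to death occurring prior to or on day D4 will be imputed in the highest category".
- Other missing values: the last available score is carried forward before the category is derived.

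The protocol describes no comparison on the uncut score.

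For the WHO COVID-19 scale, the same section also declines to treat the scale as interval, but it keeps every level: "The distribution of the 9-point ordinal scale at each post randomization time point will be compared between groups with a Cochran-Mantel Haenszel test", again with modified ridit scores and stratified by baseline. In Appendix 2, death is a separate worst level (score 8) of that scale.

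**The concern.** A scale that is not interval gives a reason to avoid comparing means. It gives no reason to merge ordered levels before a test that uses order alone. The categories therefore lose information that the chosen test could have used.

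There are two consequences. Any change that stays within one category counts as no difference. A patient who has died by Day 4 receives the same rank as every living patient in the top category, wherever the top cut falls.

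The trial has about 60 evaluable patients, and its stated aim is to estimate treatment effects for the design of later trials, so ordering that has already been collected is worth keeping.

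**Working it through.** **1. Range of the score.** The highest points in Appendix 1 are respiration 3, saturation 3, supplemental oxygen 2, temperature 3, systolic pressure 3, heart rate 3 and consciousness 3. The sum is 3+3+2+3+3+3+3 = 20, so the aggregate runs from 0 to 20.

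**2. What the test needs.** Modified ridit scores are within-stratum ranks (with midranks for ties) divided by the stratum size plus one. Only order enters, so the test applies equally to 21 levels, 22 levels with death added, or 3–4 categories. Cutting only adds ties.

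**3. The two scales side by side (section 11.5.1).**

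| | WHO scale | NEWS-2 |
|---|---|---|
| Treated as interval? | No | No |
| Test | Stratified CMH, modified ridits | Stratified CMH, modified ridits |
| Levels tested | All 9 | Threshold categories only |
| Death | Own worst level | Shares the top category with living patients |

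**4. Check of the sample-size frame.** The protocol states no power for NEWS-2. Its illustration for death rates (section 11.4) uses 30 per arm, one-sided 0.025 and an unpooled Z test:

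- 0.40 v 0.10: 0.30/√(0.24/30 + 0.09/30) = 2.860; 2.860 − 1.960 = 0.900; power 81.6%.
- 0.30 v 0.04: 0.26/√(0.21/30 + 0.0384/30) = 2.857; 2.857 − 1.960 = 0.897; power 81.5%.

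Both agree with the stated minimum of 80%, so the same arm size and alpha are used below.

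**5. Power for NEWS-2 by simulation.** From the protocol: 30 per arm, one-sided 0.025, stratified modified-ridit CMH test, strata by baseline category. Assumed, because the protocol does not give them:

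- categories 0–4, 5–6, 7+ (three) or 0, 1–4, 5–6, 7+ (four);
- mean 5–8 and SD 2.5–3;
- correlation with baseline 0.3–0.6;
- treatment shift 0.5–0.75 SD;
- deaths by Day 4 of 0–10% on placebo v 0–3% on active.

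The uncut score ranks death above every living score; the cut score puts death in the top category. Each setting had 2,000–5,000 runs, so the standard error of one power figure is at most √(0.25/2000) = 1.1 points.

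| Setting | Uncut | 4 categories (loss) | 3 categories (loss) |
|---|---|---|---|
| Mean 6, SD 2.5, shift 0.5 SD, no deaths | 51.5% | 45.5% (6.0) | 44.0% (7.5) |
| Mean 7, SD 2.5, shift 0.7 SD, no deaths | 79.4% | 69.7% (9.7) | 69.1% (10.3) |
| Mean 7, change −1, SD 3, shift 0.5 SD, no deaths | 49.7% | 45.8% (3.9) | 42.6% (7.1) |
| Mean 8, SD 2.5, shift 0.5 SD, deaths 10% v 3% | 59.2% | 43.2% (16.0) | 42.9% (16.3) |
| Mean 6, change −1.5, correlation 0.3, shift 0.5 SD | 44.5% | 43.0% (1.5) | 37.2% (7.3) |
| Mean 5, change −1.5, correlation 0.6, shift 0.75 SD | 83.1% | 80.1% (3.0) | 60.3% (22.8) |

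The last two rows are near the extremes of the grid. Across all settings, the loss is about 2–16 points with four categories and about 5–23 with three. It is smallest when scores spread over all the categories and largest when most patients sit on one side of the cuts. With no treatment effect, the rejection rate was 2.4–2.8% for every version.

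**6. Size of the top category.** With an assumed top cut of 7, the simulations place about 13–65% of patients in it at follow-up, and a death would tie with all of them who are alive. The baseline share cannot be derived. By Appendix 1, a patient with respiratory rate 25–29 (3), saturation 92–93 (2) and oxygen (2) scores 7 before the other items. But inclusion criterion 5a needs only one sign. A patient who qualifies by PaO2/FiO2 alone, with rate 20 and saturation 96 on oxygen, scores 0+0+2 = 2. One who qualifies by rate 24 alone, with saturation 96 on oxygen, scores 2+0+2 = 4.

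**The case against.** The strongest defence is that nothing here is wrong. The test is valid and pre-specified, and its type I error holds. The interval-scale remark can be read as ruling out a comparison of means, with the cut resting separately on the professional-body thresholds. Comparing recognised risk bands is a legitimate preference, and the cut-offs are left to the SAP. NEWS-2 is one of many secondary endpoints in an exploratory study that claims no power for it. Deaths also count in the primary composite, Day 40 mortality, overall survival and the uncut WHO scale.

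Most of this stands, and it limits the weight of the point. What it does not answer is why the same premise and the same test keep every level for the WHO scale but not for NEWS-2. Nor is the matter left wholly to the SAP: the protocol itself fixes the cut, the test on the cut scale and the death rule, and defers only the cut-offs.

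A reader might also infer that most patients start in the top category and so cannot worsen. The documents do not support this. No thresholds or baseline distribution are given, and some eligible patients score well below 7.

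**Conclusion.** The point holds as an avoidable loss of information on a secondary endpoint. Three parts rest on the text alone: the planned test is valid on the uncut score, the protocol already uses it on every level of another scale it does not treat as interval, and deaths up to Day 4 are tied with survivors in the top category.

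The size rests on assumptions. With 3–4 categories, 30 per arm and a shift of 0.5–0.75 SD, the loss is roughly 2–23 points of power, mostly about 4–15. The protocol supplies no thresholds, SD, effect size or Day 4 death rate, so no single figure should be read as a property of this plan. How many patients start in the top category depends on the cut and the case mix, and is unknown.

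It would also be wrong to call the planned analysis invalid, or to say that the cuts have no stated basis. Priority is low to moderate.

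**What to change.** In section 11.5.1 and the SAP, apply the same stratified CMH test with modified ridit scores to the uncut NEWS-2 aggregate at each planned time point, with death ranked one level worse than 20, and name this as the NEWS-2 comparison. Keep the threshold categories for the descriptive tables, the stacked bar plots and the baseline stratification.

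The cost is about one sentence in each document. The data and the test are unchanged, and because the last available score is already carried forward before categories are derived, the uncut variable will exist anyway. The downside is that the test no longer addresses the clinical-risk bands directly, although they are still tabulated.
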